**Hypotheses**

The efficacy of Chloroquine for the treatment of uncomplicated vivax malaria remained high in Northern Ethiopia

**Objectives**

**General objective:**

- To assess the therapeutic efficacy and safety of CQ monotherapy for the treatment of uncomplicated *vivax malaria* in Bullen district, west Ethiopia.

**Specific objectives**

- To assess the clinical efficacy of CQ among  6 months old who suffer from uncomplicated vivax malaria
- To measure the parasitological efficacy of CQ among 6 months who suffer from uncomplicated vivax malaria; and
- To assess the incidence of adverse events in vivax malaria mono infected patients who take CQ treatment

**Sample size**

The sample size will be determined using a simple population proportion formula by taking the proportion of treatment failure of the town, which is unknown. Therefore, according to WHO protocol, the value of population proportion will be 0.50, which helps to have the largest sample size for enough observations, irrespective of the actual failure rate value of the true population. So according to population proportion formula, the expected population proportion of clinical treatment failures (*P=0.5*) in the confidence interval (usually 95%), and the precision (*d*) usually 10%, this study will have 422 subjects including 10% of non-respondents.

n= (z2α/2) pq

d2

n = (1.96)2(0.5x0.5) = 384,

(0.5)2

Therefore, 422 subjects will be included in this study to have high amenable observations. However, as WHO in 2009 suggests that, to say anti-malaria therapeutic test result is representative in a given area when at least 50 and above sample size will be considered.

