Although CQ has been the cheapest and mainstay, treatment for vivax, malaria in Ethiopia, its efficacy is not well established, throughout the country. There is, little information on the response of *P. vivax* to CQ in Ethiopia. To mention them, a study conducted from Debre Zeit area in 1996, the rate of parasitological failure to CQ treatment on day 7was indicated to be 2% (n = 255)[20] and more recently an increased overall failure rate of 5.76% at same area[21]. Such growing evidences of the occurrence of CQR at varying degrees in Ethiopia necessitate further regular assessment of the drug’s treatment outcome in different setting to help support policy makers if changes in treatment policies are to be made. Therefore, in the present study, we planned to assess the efficacy of standard CQ treatment for *P. vivax* malaria in a one arm observational, prospective follow up study among patients who will be visiting the outpatient department of Bullen Health Center, Northern, Ethiopia.

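### The sample-size paragraph gives a precision of 10% and prints a denominator of 0.5 squared, but 384 and 422 follow only from a precision of 5 percentage points

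*Protocol*

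**What the plan says.** The Sample size section of the Protocol uses the single-proportion formula n = z²pq/d². Because the failure rate in the town is not known, "the value of population proportion will be 0.50", chosen to give the largest sample. Confidence is 95%.

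The same sentence names the precision d and ties it to the final number: "usually 10%, this study will have 422 subjects including 10% of non-respondents".

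The worked line then reads "n = (1.96)2(0.5x0.5) = 384", with 0.5 squared printed below it as the denominator. The section concludes: "Therefore, 422 subjects will be included in this study". It also mentions a WHO minimum of 50 but does not use it to derive the size.

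**The concern.** One short paragraph should contain one value of d. This one contains two explicit values, 10% and 0.5, and a result that neither produces.

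This matters because the precision is the only statistical property of the design that the protocol states. The Hypotheses section says only that efficacy "remained high in Northern Ethiopia" and sets no threshold, and there is no power statement. Anyone who later judges whether the day-28 failure risk was estimated as precisely as planned will compare it with a margin twice as wide as the one behind 422. For example, if recruitment fell short and 150 patients were evaluable, the stated 10% would be met but the precision that generated the sample size would not.

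**Working it through.** **Inputs, all from the Sample size section:** z = 1.96 (95%, two-sided); p = q = 0.5; d = 10% in the sentence; d = 0.5 in the printed denominator; result 384; allowance for non-response 10%; final size 422.

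**Reproducing the plan's figure.** The numerator is 1.96² x 0.5 x 0.5 = 3.8416 x 0.25 = 0.9604.

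| d used | Where it comes from | n = 0.9604 / d² | Rounded up |
| --- | --- | --- | --- |
| 0.10 | sentence | 0.9604 / 0.01 = 96.04 | 97 |
| 0.5 | printed denominator | 0.9604 / 0.25 = 3.84 | 4 |
| 0.05 | not stated in the protocol | 0.9604 / 0.0025 = 384.16 | 385 (protocol: 384) |

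Working backwards from 384, d = √(0.9604 / 384) = 0.0500.

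**From 384 to 422.** 384 x 1.10 = 422.4, which gives the stated 422. So 384 and 422 agree with each other and with d = 0.05, and with neither printed value of d.

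**Other routes to 384.** With d = 0.10, 99% confidence gives 165.9, one-sided 95% gives 67.6, and a continuity correction at two-sided 95% gives 105.8. With d = 0.5 the same variants give 6.6, 2.7 and 5.7. None comes near 384.

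**Size if 10% were meant.** 97 evaluable. Adding 10% gives 97 x 1.10 = 106.7, so 107; dividing by 0.90 gives 107.8, so 108.

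**Precision that 422 delivers.** A 10% loss leaves 422 x 0.90 = 379.8, about 380. At P = 0.5 the half-width is 1.96 x √(0.25 / 380) = 0.0503, or 5.03 points. As an illustration only, if the failure rate were near the 5.76% that the Introduction cites from another Ethiopian area, it would be 1.96 x √(0.0576 x 0.9424 / 380) = 0.0234, or about 2.3 points.

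**The case against.** The best defence is that the 0.5 is a typing slip for 0.05, and that 10% means the full width of the interval, hence a half-width of 5 points. The first half is plausible, but correcting the slip alone leaves 10% in the sentence. The second half would reconcile the sentence with 384, but the text labels the 10% as d, the quantity that the formula squares. Even on that reading the printed denominator stays wrong. Loss of superscripts when the PDF was read explains a flattened exponent, not a missing zero.

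It is also fair to say that the consequence is confined to the document. That stands, and it rules out several stronger readings that a reader might infer:

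- *The study is too small.* It is not: 422 is about four times what d = 10% requires, and it matches d = 5 points closely.
- *The intended number is unclear.* It is not: 384 and 422 are stated plainly and agree with each other. What is unclear is the precision they are meant to deliver.
- *A 10-point margin around a 5.76% failure rate would run below zero and tell nothing about efficacy.* This moves a half-width that belongs to P = 0.5 and 97 patients onto a different rate. At 5.76%, 97 patients would give 1.96 x √(0.0576 x 0.9424 / 97) = 0.046, or about 4.6 points. A 10-point margin there corresponds to 0.2085 / 0.01 = 20.9, so 21 patients (0.2085 = 1.96² x 0.0576 x 0.9424), which nobody proposes.
- *The plan should have been sized on its own local rates.* The 2% and 5.76% in the Introduction come from the Debre Zeit area, and the 2% is day-7 parasitological failure. The protocol calls the town's rate unknown and takes P = 0.5 as a deliberate conservative choice, which is legitimate.
- *The 10% allowance is materially short.* Dividing by 0.90 gives 384 / 0.90 = 426.7, so 427 instead of 422, but the half-width changes only from 5.00 to 5.03 points.

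**Conclusion.** The point holds as a contradiction within the sample-size statement. The stated precision (10%) and the printed denominator (0.5 squared) are both wrong for the planned 422; the value that generates it is 5 percentage points. The error is a factor of 2 in d and 4 in n for the sentence, and a factor of 10 in d and 100 in n for the printed formula. The planned number is clear and sufficient for either 5 or 10 points, to within 0.03 of a point for the former, so neither recruitment nor patients are affected.

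The conclusion rests on the protocol's own formula, z = 1.96 and P = 0.5. The half-widths treat the outcome as a simple proportion among evaluable patients. The Kaplan-Meier estimate that the protocol plans may differ slightly with censoring, but this does not bear on the contradiction.

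**What to change.** In the Sample size section:

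1. Keep 384 and 422.
2. Replace the stated precision of 10% with 5 percentage points at P = 0.5.
3. Print 0.05 squared as the denominator of the worked formula.
4. Optionally, add that a 10% loss leaves about 380 evaluable patients, with a half-width of 5.03 points at P = 0.5. As an illustration only, the half-width would be about 2.3 points if the failure rate were near 5.76%.

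If the investigators did intend 10%, the size should be derived from that instead: 97 evaluable and about 107 to 108 enrolled, with 0.10 squared in the formula.

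The first course costs the rewording of one paragraph. It needs no additional patients and no change to the visits or the analysis.

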**Measurements**

**Variables**

**Dependant variables**

- A 28 days of CQ efficacy/clinical and parasitological outcome after treatment through the following methods:
- **Hemoglobin concentration:** Hemoglobin will be determined through Hem cue heamatological analyzer or through haematocrit at days of 0, and 28 of time schedule to check the improvement of the patients’ heamoglobine level, which indicates indirect evaluation of the drug efficacy.
- **Clinical signs and symptom consideration:** the clinical outcome of patients after treatment will be assessed and recorded according to the protocol of WHO (2009).
- **Parasitic loads:** Parasitic load will be quantitate according to the schedule of WHO protocol (day 0, 1, 2, 3, 7, 14, 21and 28 day), and will help for the classification of the drug response.
- Early Treatment Failure (ETF)
- Late Clinical Failure (LCF)
- Late Parasitogical Failure (LPF)
- Adequate Clinical and Parasitological Response (ACPR)
- **Time to fever clearance (FCT)**: Time to fever clearance will be record according to the WHO protocol.
- **Safety and tolerability**: The incidence of any adverse event will be documented. All patients will be asked routinely about previous symptoms and about symptoms that have emerged since the previous follow-up visit through checklists. When clinically indicated, patients will be evaluated and treated appropriately. All adverse events will be recorded on the case report form.

**Independent variables**

- **Socio-demographic variables:** Questionnaire will be developed which can assess sex, age, and educational status with socio-economic status of the population.
- **Body weight:** Body weight will be recorded on day 0 to the nearest kilogram on a Salter scale or on a hanging scale for young children.

**Data /sample collection**

Capillary Blood collection will done by the senior laboratory technicians who have long time experience, for screening (whether the subjects are *p.vivax* positive or not) and if the sample is positive, the person will be asked for his/her consent to participate in the study up to end. After having the consent blood will be run for hematological procedure (heamoglobine determination) for 0, and 28 days and for thick and thin blood smear preparation according the schedule of the study.

**Quality control**

Clinical examination and parasite counts will be perform every day for two consecutive days whether the parasites and symptoms are completely cleared or not and continuous check up will be perform weekly from day 7 of the first drug administration till 28 days of total follow up days. Axillary temperatures will record every day of the first two days during blood sample collection. Primary end points of the study are the parasitological and clinical response to treatment. All slides on day 0, all positive slides after day 7 (regardless of the parasite species) and 10% randomly selected negative slides will crosschecked by a senior laboratory technician who are engaged in the regional laboratory. The machine that can measure heamoglobin will be calibrated and adjust through standards and, reagents like Giemsa stains will be check by the known positive samples. In addition, for the laboratory technicians, if necessary refreshment course on the identification and enumeration of the parasites will be provide.

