**Abstract**

**Background**

Emergence, of resistance to anti-malarials is a major challenge for effective malaria control in sub-Saharan Africa. Extensive use of chloroquine (CQ) as a monotherapy led to significant increase in levels of resistance across many malaria-endemic countries, including Ethiopia. Thus continuous and regular monitoring of drug efficacy is critical for establishing rational anti-malarial drug policies. This study therefore, assesses the therapeutic efficacy of Chloroquine(CQ) for the treatment of *Plasmodium vivax* infectionsin Northwestern, Ethiopia. **Methods**

An observational, prospective 28-days in vivo therapeutic efficacy evaluation will be conducted from July to December, 2014, in Northwest Ethiopia at Bullen health center. Patients confirmed to have monoinfection of vivax malaria, aged above 6 months will be enrolled. All subjects will be then treated with standard Chloroquine(25 mg/kg for three (3) days). Parasitological and clinical outcomes of treated patients will be evaluated prospectively on days 1, 2, 3, 7, 14, 21, and 28 during the entire follow-up period.. Data will be entered and analyzed using SPSS version 20. Kaplan-Meier survival estimate will be used to analyze therapeutic failure rate during follow-up period. The initial study endpoint will be taken as the risk of failure at 28 days by survival analysis. Changes in fever and parasite clearance will be evaluated at each follow up visit. Changes in mean haemoglobin concentrations will be computed on days 0 and 28 and quantitative variables will be compared using paired *t* test. P value of < 0.05 will be considered a significant level.

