**Operational definitions and study end points/outcomes**

**Early treatment failure (ETF):** includes any of the following:

• Development of danger signs or severe malaria on Day 1, Day 2 or Day 3, in the presence of parasitaemia

• Parasitaemia on Day 2 higher than Day 0 count irrespective of axillary temperature

• Parasitaemia on Day 3 with axillary temperature ≥37.5 °C

• Parasitaemia on Day 3 ≥ 25% of count on Day 0.

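### The Quality control schedule stops axillary temperature after the first two days, against the protocol's own Day 3 visit and the Day 3 fever rule for early treatment failure

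*Protocol*

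**What the plan says.** Protocol, Quality control, sets the early schedule in two sentences. On examination and counts: "Clinical examination and parasite counts will be perform every day for two consecutive days", after which "continuous check up will be perform weekly from day 7 of the first drug administration till 28 days". On temperature: "Axillary temperatures will record every day of the first two days during blood sample collection". The same section names the parasitological and clinical response as the primary end points.

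Other parts of the Protocol give a different schedule:

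- The Abstract has outcomes evaluated "on days 1, 2, 3, 7, 14, 21, and 28" and adds: "Changes in fever and parasite clearance will be evaluated at each follow up visit".
- Measurements (Parasitic loads) lists counts on days 0, 1, 2, 3, 7, 14, 21 and 28.
- Annex 1, Microscopic blood examination, lists follow-up films on days 2, 3, 7, 14, 21 and 28.

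Operational definitions and study end points/outcomes gives four rules for early treatment failure:

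1. "Development of danger signs or severe malaria on Day 1, Day 2 or Day 3", with parasites present.
2. "Parasitaemia on Day 2 higher than Day 0 count irrespective of axillary temperature".
3. "Parasitaemia on Day 3 with axillary temperature" at or above 37.5 °C.
4. A Day 3 count of at least 25% of the Day 0 count.

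The same section defines fever clearance as a fall below 37.5 °C that is sustained for 48 hours or more.

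**The concern.** Early treatment failure is one of the outcome classes that make up the 28-day failure risk, and its third rule can be applied only if axillary temperature is taken on Day 3. Quality control is the one place that names days as a schedule for taking follow-up temperatures, and it stops before Day 3. The Abstract promises a fever assessment at each visit, and Measurements refers fever clearance to the WHO protocol without naming days. Staff who look for the temperature schedule will therefore find an instruction that is too short for the endpoint.

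The resulting error runs one way. Without the Day 3 temperature, a true early failure can be recorded as a success or as a later failure. A true success cannot become a failure. The bias is toward the Protocol's stated hypothesis that chloroquine efficacy has remained high.

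**Working it through.** The Protocol has no figure of its own to reproduce here. The check compares days scheduled with days needed.

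**Days scheduled**

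| Section | Item | Days |
| --- | --- | --- |
| Quality control | axillary temperature | first two days (0–1 or 1–2) |
| Quality control | examination and counts | two consecutive days, then 7, 14, 21, 28 |
| Abstract | outcome evaluation, fever at each visit | 1, 2, 3, 7, 14, 21, 28 |
| Measurements | parasite load | 0, 1, 2, 3, 7, 14, 21, 28 |
| Annex 1 | films after day 0 | 2, 3, 7, 14, 21, 28 |

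Whether the first day is called Day 0 or Day 1, the first two days end at Day 1 or Day 2. The temperature sentence does not reach Day 3.

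**Days needed for early treatment failure, if films follow Measurements and Annex 1 and temperature follows Quality control**

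- Rule 1 (danger signs, Days 1 to 3, with parasitaemia) turns on clinical signs and a film. It does not need a temperature reading.
- Rule 2 (Day 2 count above Day 0) needs two counts and no temperature. Both counts are available.
- Rule 3 (Day 3 parasitaemia with temperature of at least 37.5 °C) needs a Day 3 temperature. None is available.
- Rule 4 (Day 3 count at least 25% of Day 0) needs two counts and no temperature. Both are available.

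One rule of four is left without data.

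**Who changes class**

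Take a patient with Day 3 parasitaemia, temperature of at least 37.5 °C, a count below 25% of Day 0 and no other early-failure criterion.

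- If the patient is clear from then to Day 28, late clinical failure (Day 4 onward) and late parasitological failure (Day 7 onward) do not apply either. The patient meets the definition of an adequate response, so a failure is scored as a success.
- If the patient is parasitaemic again on a scheduled film on Days 7 to 28, a failure is still recorded, but later and in another class. The 28-day total does not change.

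**Size per misclassified patient**

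With complete follow-up the Kaplan-Meier failure risk at Day 28 equals failures divided by patients. With the planned 422, one lost failure lowers it by 1/422 = 0.00237, or 0.24 percentage points. If only the 384 before the 10% allowance contribute, it is 1/384 = 0.00260, or 0.26 points.

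**Fever clearance**

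Two daily readings are about 24 hours apart. The definition needs at least a further 48 hours below 37.5 °C after the first such reading, and 24 < 48. If the next reading is at the Day 7 check-up, the intervening days are unobserved.

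**The case against.** The strongest reply is that the Protocol already requires Day 3. The Abstract lists it and has fever evaluated at each visit, two sections schedule the Day 3 film, and the failure definition itself calls for a Day 3 axillary temperature. Quality control does not say that temperature is taken only on the first two days, and its examination sentence could be read as a minimum period of daily checks. On this view harm arises only if staff follow one loosely worded sentence against the visit list and the outcome definitions. Much of this stands: the intended schedule can be recovered. What remains is that the one sentence naming days for temperature readings gives the wrong ones.

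A reader might infer more than the documents support:

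- **That the trial has no Day 3 visit.** The Abstract, Measurements, Annex 1 and the failure definitions all show that one is intended.
- **That two or three of the four rules are lost.** This would require staff to disregard both explicit film schedules. If the Day 3 film is taken, the 25% rule works without temperature.
- **That the examination sentence must exclude Day 3.** The Introduction and the dosing chart call the first dose Day 1. On that numbering, two consecutive days of follow-up after the first dose are Days 2 and 3. The argument therefore rests on the temperature sentence.
- **That the failure total after Day 7 is also wrong.** The weekly check-ups may include temperature. If they do not, late clinical and late parasitological failure would be hard to separate, but parasitaemia on Days 7 to 28 is a failure in either class.
- **That the failure rates quoted in the Introduction show how many patients are affected.** One is parasitological failure at day 7 and the other an overall rate, both from another area. Neither measures fever with parasitaemia on Day 3.

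It is also fair to say that one misclassified patient moves the estimate little beside the 10% precision stated under Sample size.

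**Conclusion.** The point holds as an internal inconsistency that should be fixed. As written, the Quality control temperature sentence contradicts the Abstract's visit schedule. If followed, it leaves one of four early-treatment-failure rules without data and the 48-hour fever-clearance definition unsupported.

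The effect on the primary result is one-directional: about 0.24 percentage points of overstated efficacy for each patient who meets only the Day 3 fever rule and then stays clear to Day 28. That figure assumes 422 patients with full follow-up, Day 3 films taken as scheduled elsewhere, and temperature taken as Quality control says. The documents give no frequency for such patients, so no total bias can be stated; if sites follow the Abstract instead, it is zero.

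**What to change.** The text is wrong as written. Reword Quality control so that clinical examination, blood film and axillary temperature are all done on Days 0, 1, 2, 3, 7, 14, 21 and 28 and at any unscheduled visit, and state there that Day 0 is the day of first dose.

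The cost is an edit to one section. No visit is added beyond those in the Abstract and Measurements, and neither dose nor sample size changes. The day labels in the dosing chart and the absence of Day 1 from the Annex 1 film list are separate matters, and this correction does not depend on them.

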**Data analysis**

Data will check for its completeness before entering for analysis. Then it will be entered after edited and cleaned in to SPSS 20.0 version for analysis. The overall CQ efficacy will be determined and recorded through the help of descriptive and inferential method of data analysis. Simple frequencies will be applied to see the distribution of the socio demographic characteristics of independent variables. Kaplan-Meier survival estimate will be used to estimate therapeutic failure risk during follow-up period. The mean difference, in haemoglobin/hematocrit level on days 0 and 28 and quantitative variables will be compared using paired *t* test. P-value less than 0.05 will take as statistical significance association and 95% CI of Odds ratio for the strength of the statistical associations. Then it will code and transcribed manually from the notes and recorded and will supplement to the results of the qualitative study accordingly.

